## Study aims

The overall aim of both randomised controlled trials (RCT) is to investigate the efficacy and acceptability of using high-frequency, low-load BFR-RT in UK military personnel with lower limb MSKI where persistent pain is the primary limiting factor for progression.

### Phase One RCT

A 1-week pilot RCT will determine the most effective and acceptable BFR-RT protocol in UK military patients, with the primary aim of reducing pain. This will be achieved by comparing two different BFR-RT pressures (high-pressure (80% LOP) vs low-pressure (40% LOP)) within a military residential rehabilitation setting. It is hypothesised that high-pressure BFR-RT will elicit a greater hypoalgesic response, but be less tolerable (ie, less total work completed with higher perception of effect).

### Phase Two RCT

A 3-week RCT (resembling actual inpatient rehabilitation duration at DMRC) will compare the efficacy of the most clinically acceptable BFR pressure from Phase One to standard/conventional UK Defence Rehabilitation residential rehabilitation practice on physiological mechanisms underpinning changes in pain modulation and rehabilitation outcomes. It is hypothesised that the BFR-RT group will have greater reductions in pain, and increases in function, when compared with usual care alone.

## Methods and analysis: shared

### Study setting

Both phases of the study will be conducted at DMRC, Stanford Hall. The facility delivers 3-week residential rehabilitation courses to service personnel with complex/chronic injuries. The exercise rehabilitation components of each course are led by a physiotherapist and exercise rehabilitation instructor who receive specific training to ensure continuity, and best practice across UK Defence Rehabilitation. Details of course components are outlined in table 1. The experimental treatment group interventions will be delivered alongside a standardised rehabilitation programme (replacing the knee dominant exercises; leg press and knee extension).

**Table 1 T1:** Components of residential rehabilitation at Defence Medical Rehabilitation Centre, Stanford Hall

*Course component*	*Intervention content*	*Intervention aim*	*Frequency and duration*
SEM/Rehabilitation Medicine Consultant Review	Clinical ReviewMedication ReviewPatient education for example, diagnostic description+/-support of imagingCo-ordination of investigation and referralLiaison with primary, secondary care and occupational health	Optimisation of health stateConsideration of co-morbiditiesConsideration of need for further investigations or imaging, for example, POCUS, MRI, X-ray etc.Consideration of need for further sub-specialist referral, for example, psychological support, neurophysiology, specialist pain teamRecommendations for occupational function and follow-up	Day one course reviewDischarge clinic on final day of courseInterim 1-2-1 or MDT course reviews as requiredTypical appointments 30 min
Individual Patient Assessment	MDT ClinicSubjective AssessmentObjective Assessment	Identify individual impairments and dysfunction to be addressed within the residential rehabilitation course	1× 1-hour session
Exercise-BasedTherapy (Group)	ERI led group-based training that involves cardiovascular exercise, functional movement patterns, hydrotherapy, minor team games, LL mobility, neuromuscular control, balance and proprioception, and LL strengthening	Improve muscle strength, and quality and timing of movement; increase joint range of motion; induce relaxation; promote normal walking gait; reduce pain levels	15× 45 min sessions
Exercise-BasedTherapy (Individual)	ERI/PT led individual, directly supervised, gym-based session compromising of elements of group-based session	As per group-based therapy	4× 1-hour sessions
Patient Education	Workshops and presentations covering anatomy and pathology of their lower limb injury, goal setting, nutrition, pain education science, planning and pacing, and principles of exercise	Improve ability to relax, and knowledge of self-help techniques and treatment options; improves patients understanding of injury, diagnosis and rehabilitation plan; promote behavioural change; reduction of pain; weight management	5× 30 min sessions
One-on-One Support	Individualised PT and/or OT sessions focusing on active/passive ROM exercises, advice on home exercise, cognitive behavioural therapy techniques, gait re-education training, manual therapy techniques, muscle activation and timing patterns, pain management, postural re-education, relaxation techniques, and self-help coping strategies	Control and reduce pain; improve muscle strength, and quality and timing of movement; increase joint ROM; induce relaxation; promote behavioural change and normal walking gait	5× 30 min sessions

ERI, exercise rehabilitation instructor; LL, lower limb; MDT, multidisciplinary team; OT, occupational therapy; POCUS, point-of-care ultrasound; PT, physiotherapy; ROM, range of movement; SEM, sport and exercise medicine.

### Ethics and dissemination

The study has been approved by the Army Scientific Advisory Committee and Ministry of Defence research ethics committee (2318/MODREC/24), Northumbria University, and is registered with clinicaltrials.gov (trial registration number: Phase One, NCT06621914; Phase Two, NCT06621953). The study sponsor is the Director of Research within UK Defence Medical Services. The study is jointly funded through the Defence Medical Services Research Steering Group, Delfi Medical Innovations Inc. and Northumbria University. The study protocol has been developed in accordance with the Standard Protocol Items for Randomised Trials (SPIRIT) statement^51^ (SPIRIT checklist found in online supplemental file 1) and the RCT will be delivered in accordance with Consolidated Standards of Reporting Trials (CONSORT) 2010 Statement: updated guidelines for reporting parallel group randomised trials.^52^ The results of these studies will be published by the investigators in relevant scientific peer-reviewed journals, regardless of study outcomes. Moreover, study results will be presented at relevant scientific conferences.

### Participants, recruitment and screening

All patients referred to DMRC, Stanford Hall multidisciplinary injury assessment clinic with MSKI of the lower limb with persistent pain as the primary limiting factor for progression will be screened against the eligibility criteria (table 2) by a sport and exercise medicine and/or rehabilitation medicine consultant within the lower limbs team who is not responsible for the direct treatment of the participant while on the residential rehabilitation course. Those who meet the eligibility criteria will be contacted via telephone by a member of the research team to discuss their possible inclusion in the study. Potential participants will be sent an information pack consisting of the patient information sheet. Participants who meet the eligibility criteria and provide written informed consent (returned to a member of the research team; online supplemental file 2) will be randomly assigned to one of the two study groups. Participants will then be invited to a pre-admission clinic to collect baseline outcome measures.

**Table 2 T2:** Participant inclusion/exclusion criteria

*Inclusion*	*Exclusion*
Serving UK military personnel, Aged 18–55, Has unilateral lower limb injury whereby pain is the primary limiting factor hindering progression, as diagnosed by relevant consultant and team, Reduced occupational employability and function, Scheduled to attend Defence Medical Rehabilitation Centre, Stanford Hall, for 3-week residential rehabilitation course	Musculoskeletal-specific exclusion criteria Any medical contraindication related to blood flow restriction exercise* Non-musculoskeletal or serious pathological condition (ie, inflammatory arthropathy, infection or tumour) Spinal or referred pain from non-local pain source Any pre-diagnosed physical impairment or comorbidities (including cardiovascular disease) precluding the safe participation in the rehabilitation programme and/or assessment procedures Cortico-steroid or analgesic injection intervention to the affected area within the previous 7 days Currently pregnant or have not yet completed a return to work assessment following the birth of your child *Medical-related exclusion criteria History of cardiovascular disease (hypertension, peripheral vascular disease, thrombosis/embolism, ischaemic heart disease, myocardial infarction) History of the following musculoskeletal disorders: rheumatoid arthritis, avascular necrosis or osteonecrosis, severe osteoarthritis History of the following neurological disorders: Alzheimer’s disease, amyotrophic lateral sclerosis, peripheral neuropathy, Parkinson’s disease, severe traumatic brain injury Varicose veins in the lower limb Acute viral or bacterial upper or lower respiratory infection at screening Known or suspected lower limb chronic exertional compartment syndrome Surgical insertion of metal components at the position of cuff inflation History of any of the following conditions or disorders not previously listed: diabetes, active cancer History of elevated risk of unexplained fainting or dizzy spells during physical activity and/or exercise that causes loss of balance Increased risk of haemorrhagic stroke, exercise-induced rhabdomyolysis

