### Randomisation and blinding procedure

For both phases, a permuted block randomisation method with a 1:1 ratio will be used using random block sizes. Randomisation will be stratified by age (18–36, 37–55 years old) and sex, to prevent an imbalance between groups.^53^ A plain language statement will inform participants that they have an equal chance of receiving low-load RT with either high-pressure or low-pressure BFR (Phase One), or low-load RT with BFR or standard rehabilitation (Phase Two). A sealed envelope will be opened to reveal group allocation by an independent administrator not involved in the recruitment, treatment or assessment of study outcomes. Given the nature of BFR, it is not feasible to blind participants to their treatment allocation. The clinical staff who deliver the study interventions and collect outcome data for the RCT must also be, by necessity, unblinded.

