**Figure 1 F1:**
[figure not shown]
Study design flow diagram: Phase One. Phase One timepoints—T0_P1_, baseline (day −3); T1_P1_, admission day (day 1); T2_P1_, daily (days 1–5); T3_P1_, end of intervention (day 5); T4_P1_, follow-up (day 6). BFR40, blood flow restriction with resistance training at 40% limb occlusion pressure; BFR80, blood flow restriction with resistance training at 80% limb occlusion pressure; DMRC, Defence Medical Rehabilitation Centre.

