Pressure pain threshold testing will be completed at T0_P1_, T1_P1_, T2_P1_, T3_P1_ and T4_P1_. At each location, two measures will be collected, separated by 20 s, with the mean score for analysis (PPT quantified as the kilogram force applied at the point of ‘pain’). Thereafter, PPT testing will be completed pre-intervention, immediately post-intervention and 60 min post-intervention to assess the immediate and lasting effects of the intervention. Additionally, the pre-intervention PPT metrics on the following day will act as a 24-hour mechanistic measure of BFR-induced hypoalgesia following BFR intervention. As a result of assessing six separate points, we will be able to determine if the BFR interventions produce a systemic as well as a local hypoalgesic effect.

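### Random assignment is written ahead of the T0 baseline visit, and nothing says allocation is withheld until T0 is complete, so baseline measures are exposed to knowledge of allocation

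*Protocol article*

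**What the plan says.** The section on participants, recruitment and screening, which applies to both phases, states that those who are eligible and consent "will be randomly assigned to one of the two study groups. Participants will then be invited to a pre-admission clinic". The second of these sentences goes on to give the clinic's purpose: "Participants will then be invited to a pre-admission clinic to collect baseline outcome measures". The figure legends date T0 at day −3 and admission at day 1.

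The section on randomisation and blinding says that "it is not feasible to blind participants to their treatment allocation", and adds: "The clinical staff who deliver the study interventions and collect outcome data for the RCT must also be, by necessity, unblinded". On disclosure it says: "A sealed envelope will be opened to reveal group allocation by an independent administrator". That person takes no part in recruitment, treatment or outcome assessment. No time relative to T0 is given for opening the envelope or for telling participants and assessors.

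The T0 measures are set out in several places:
- PPT, Phase One: "Pressure pain threshold testing will be completed at T0_P1_, T1_P1_, T2_P1_, T3_P1_ and T4_P1". In Phase Two it also runs from T0 to T4.
- 5RM strength: T0 and T4 in both phases.
- BPI, LEFS and injury-specific questionnaires: T0, T3 and T4 in Phase Two. For Phase One the article refers to a supplement not shown. The sample size section counts a pre-intervention measure among its three timepoints.
- Isometric mid-thigh pull: T0 in Phase Two, but first at T1 (admission day) in Phase One.

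**The concern.** Lack of blinding during treatment cannot be avoided with a pressure cuff. At baseline it can be, because a participant who has not yet been allocated has no allocation to know. The order as written gives that protection away.

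The measures at risk are the ones that knowledge can move. BPI and LEFS are self-reported. PPT is the moment at which the participant says that the pressure hurts, with a member of staff applying it. 5RM depends on effort. In Phase Two, expectation among those offered BFR and disappointment among those offered usual care could plausibly differ.

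Baseline also carries weight in the decisions. It is one level of the planned between/within ANOVA. The Phase One rule for choosing the Phase Two pressure uses the reduction in BPI and then the improvement in LEFS, so a distorted starting value could carry into the next trial. Finally, a participant who withdraws between assignment and T0 is randomised without any baseline, and such losses may be unequal between arms.

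**Working it through.** The protocol gives no figure for this point. The check is one of sequence, followed by arithmetic on what a baseline shift would do.

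**Sequence.** Recruitment section: consent, then assignment, then the clinic for baseline measures. Blinding section: participants and outcome collectors unblinded, with no exception stated for T0. Nothing in the text shown reverses the order or delays disclosure. The stratifiers are age and sex, both known before T0, so stratification does not require randomising earlier.

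**Effect of a baseline shift.** Let *s* be the difference between arms in baseline BPI caused by knowing the allocation, with later scores unaffected. The document gives no value for *s*; 0.25 to 1.0 points is an assumption. The 2-point minimally important difference is from the Phase One section on patient-reported outcomes.

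- *Pre-to-post group contrast* (difference in change): the error has size *s*.
  - 0.25/2 = 12.5%; 0.5/2 = 25%; 1.0/2 = 50% of the important difference.
- *Group effect averaged over m timepoints* (the between-factors form used for sample size): the error is *s/m*.
  - Phase One, m = 3: 0.25/3 = 0.08 to 1.0/3 = 0.33 points.
  - Phase Two, m = 4: 0.25/4 = 0.06 to 1.0/4 = 0.25 points.
- *Baseline-adjusted contrast with slope b*: the error is *b × s*. With b = 0.5 (assumed) it is 0.5 × 0.25 = 0.125 to 0.5 × 1.0 = 0.5 points. With s = 0.5, slopes of 0.3 to 0.7 (assumed) give 0.15 to 0.35 points. The slope equals the pre/post correlation only if the two SDs are equal.

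The direction differs. If baseline pain is pushed up in one arm, that arm's improvement is exaggerated in the change contrast, but its average pain looks worse in the averaged effect. The analysis section follows up significant two-way interactions, and the hypotheses concern reductions in pain, so the change contrast is the more relevant one.

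**Loss before T0.** One participant is 1/28 = 3.6% of Phase One or 1/26 = 3.8% of Phase Two. Each phase allows for four losses in total (28 − 24 and 26 − 22). The protocol gives no rate of loss before T0, so no expected number can be derived.

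**The case against.** The strongest objection is that being assigned is not being told. The protocol treats opening the envelope as a separate act by an independent person and does not date it. Its reasons for not blinding concern receiving and delivering BFR, which does not happen at day −3. A reader might infer that nobody is blinded at the baseline visit; the documents do not establish this. It is an inference from two sections read together. This part of the objection stands, but it does not remove the point: the blinding statement makes no exception for T0, and the order as written leaves the door open.

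A reader might also infer that Phase One BPI and LEFS are taken at T0. The Phase One baseline section does not list them, and their schedule is in a supplement not shown. Only a pre-intervention BPI is implied. Nor can the flow diagrams be called wrong, since they are not shown.

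On size, no bias of a given magnitude is demonstrated, and its direction is unknown. If knowing the allocation moved later reports by the same amount, the shift would cancel in the change contrast. Differential withdrawal before T0 is possible but has no figure behind it, and four losses per phase are already allowed for. The protocol also plans to report missing data and to use multiple imputation as a sensitivity analysis, though for someone lost before T0 there would be no observed pain score to start from.

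Last, the larger weakness, unblinded self-reported follow-up, remains whatever is done here and is openly acknowledged. In Phase One both arms receive BFR, so expectation differs only by pressure. Phase One was scheduled for October 2024 to August 2025 and may be past amendment. These facts limit what the change achieves but are no reason to leave an avoidable exposure in place.

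**Conclusion.** The point holds as one of sequence and missing safeguard. The text places assignment before T0, declares participants and outcome collectors unblinded, and does not withhold allocation until T0 is complete. PPT and 5RM in both phases are exposed, as are BPI and LEFS at T0 in Phase Two. The Phase One mid-thigh pull, first taken on admission day, also follows assignment.

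The possible size is 12.5% to 50% of the 2-point important difference in the pre-to-post contrast, for an assumed differential shift of 0.25 to 1.0 points that does not persist to follow-up. It is a third or a quarter of that in an effect averaged over three or four timepoints. This rests on allocation being known at T0, which is inferred. If allocation is in fact held back, the distortion goes and the remedy is a sentence saying so.

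**What to change.** Reorder the recruitment section: eligibility, consent, all T0 measures completed and signed off, then the independent administrator opens the envelope, with allocation revealed before the first session. State in the randomisation section that participants and assessors do not learn the allocation until T0 is signed off. Revealing it after the admission-day tests, where practical, would also cover the Phase One mid-thigh pull. Align the flow diagrams if they show the present order.

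For participants already enrolled in either phase, report when allocation was disclosed relative to T0, and report losses between assignment and T0 by arm.

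The cost is a minor procedural amendment. T0 is already a separate visit before admission, the administrator is already in place, and the stratifiers are known beforehand. Visits, staff and sample size do not change. The administrator does have to act in the interval between T0 and the first session.

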### Randomisation and blinding procedure

For both phases, a permuted block randomisation method with a 1:1 ratio will be used using random block sizes. Randomisation will be stratified by age (18–36, 37–55 years old) and sex, to prevent an imbalance between groups.^53^ A plain language statement will inform participants that they have an equal chance of receiving low-load RT with either high-pressure or low-pressure BFR (Phase One), or low-load RT with BFR or standard rehabilitation (Phase Two). A sealed envelope will be opened to reveal group allocation by an independent administrator not involved in the recruitment, treatment or assessment of study outcomes. Given the nature of BFR, it is not feasible to blind participants to their treatment allocation. The clinical staff who deliver the study interventions and collect outcome data for the RCT must also be, by necessity, unblinded.

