### Experimental intervention

During the first week of the residential rehabilitation course, participants in both groups will replace standardised knee dominant exercise with low-load BFR-RT at either low (ie, 40% LOP) or high (ie, 80% LOP) pressure, with previous literature reporting significant hypoalgesia following BFR exercise at both high and low pressures.^43 44^ Both experimental groups will complete seven BFR-RT sessions over the first week of the residential rehabilitation course (Monday–Friday). Using the Personalised Tourniquet System for BFR (Delfi Medical Innovations Inc, Vancouver BC, Canada), with an Easi-Fit BFR Cuff (single-bladder, contoured) fully encircling the limb and matching limb protection sleeve (24″×4.5″ or 34″×4.5″, dependent on limb size), each session will consist of a unilateral leg press exercise (Technogym, Bracknell, UK), followed by unilateral knee extension exercise with ankle weights (Komodo Sports, Huntingdon, UK), on the affected limb. The Personalised Tourniquet System for BFR automatically measures the individual’s LOP while at rest in supine (20–350 mm Hg±6 mm Hg of a set-point, 10 s average under non-transient conditions), which literature reports as a valid and reliable measure;^57^,^59^ thereafter, either 80% LOP (BFR80) or 40% LOP (BFR40) will be used based on the participants’ assigned group. Participants will complete 1 set of 30 repetitions, followed by 3 sets of 15 repetitions at 20% 1RM, with 30 s rest between sets (continuous inflation during exercise) and a 3 min reperfusion period between exercises. Both exercises will be performed using a 1:0:1 tempo (1 s concentric phase, no pause and 1 s eccentric phase). On the Wednesday and Thursday of the intervention week, BFR-RT will be performed twice daily, with sessions separated by >4 hours.

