#### Pressure pain threshold testing

Pressure pain threshold (PPT) testing is reported as the minimum pressure applied to cause pain and used to quantify pain sensitivity in persistent pain populations.^70^ It is suggested that PPT could be used as an indicator of persistent pain, as a reduction is consistent with hyperexcitability in central nervous system processing.^71^ The inter-rater and intra-rater reliability of PPT has previously been established as good to excellent, despite significant variation between measurement procedures being reported within the literature.^72^,^75^ For the collection of data within this pilot RCT, a member of research staff skilled in using a handheld pressure algometer (1 cm^2^ probe, Wagner Instruments, Greenwich, USA) will apply pressure at a rate of 1 kgf/s until the first point of perceived pain, whereby the participant will say ‘pain’ to indicate the perceived pain. The selected locations of measurement are based on existing literature:^43 44^

Bilateral quadriceps—test location measured 20 cm proximal to base of patella.Dominant biceps brachii—test location measured 10 cm proximal to the cubital fossa.Medial gastrocnemius of the injured/dominant limb—test location measured at 60% length of gastrocnemius muscle, measuring from calcaneus to popliteal fossa.Nondominant upper trapezius—test location measured at 10 cm from the acromion in direct line with the neck.Tibialis anterior of injured/dominant limb—test location measured at one-quarter of the distance between the superior edge of the fibular head and the most lateral part of the lateral malleolus was marked using a delible pen; then, half the distance from the palpated anterior-lateral edge of the tibia horizontal to the first mark is marked with a delible pen as testing location.

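### The reason given for not blinding participants fits Phase Two but not Phase One, where the arms differ only in cuff pressure; partial masking there is possible and cheap

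*Protocol article*

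**What the plan says.** The section on randomisation and blinding, under the methods shared by both phases, states: "Given the nature of BFR, it is not feasible to blind participants to their treatment allocation". It adds: "The clinical staff who deliver the study interventions and collect outcome data for the RCT must also be, by necessity, unblinded". Neither sentence distinguishes the phases. The same section says Phase One participants are informed beforehand that they may receive either of two BFR pressures with equal chance.

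The Phase One Experimental intervention section says that "participants in both groups will replace standardised knee dominant exercise with low-load BFR-RT at either low (ie, 40% LOP) or high (ie, 80% LOP) pressure". The tourniquet system first measures each person's limb occlusion pressure (LOP) automatically; "thereafter, either 80% LOP (BFR80) or 40% LOP (BFR40) will be used based on the participants’ assigned group".

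The Phase Two Experimental intervention section makes the choice of pressure depend on Phase One: first on the BPI, then on the LEFS if pain does not differ significantly, and otherwise on a default to low pressure.

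**The concern.** The nature of BFR is a good reason why a patient cannot be blinded to having a cuff or not having one. It says nothing about which of two inflation pressures a patient with a cuff has been given. The article applies the one reason to both comparisons and offers none specific to Phase One.

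This matters because of what the Phase One comparison decides. Its primary outcome is a pain questionnaire that the patient completes, and the second selection criterion is also a questionnaire. The study aims state a directional hypothesis: high pressure should relieve pain more but be less tolerable. A patient who knows the label, and perhaps the expected direction, may answer accordingly. Any shift of that kind enters the BPI and LEFS contrast that fixes the Phase Two pressure. Neither the strengths and limitations list nor the limitations section of the Discussion mentions lack of blinding.

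**Working it through.** No figure in the plan decides this point. The check is a comparison of sections, followed by one illustration under stated assumptions.

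**1. What differs between arms in each phase**

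| Element | Phase One: BFR40 vs BFR80 | Phase Two: BFR vs control |
|---|---|---|
| Cuff and tourniquet system | Same | BFR arm only |
| LOP measurement | Same automatic procedure | BFR arm only |
| Knee-dominant exercise | Same leg press and knee extension in place of the standard ones | Replaced in BFR arm only |
| Load and repetitions | Same: 20% 1RM; 30, then 3 × 15 | Follows the BFR protocol in BFR arm only |
| Rest and tempo | Same | Follows the BFR protocol in BFR arm only |
| BFR sessions | 7 in each arm | 21 vs none |
| Set pressure | **40% vs 80% LOP** | One pressure vs none |

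In Phase Two the patient sees the difference. In Phase One the only difference is a setting on the device.

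**2. Which outcomes each kind of masking could protect**

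- BPI (primary; first selection step): patient-administered, so only participant masking helps.
- LEFS (second selection step): completed by participants, so again only participant masking helps.
- Pressure pain threshold (PPT): ends when the patient says they feel pain under hand-applied pressure, so both patient and tester can influence it. The tester is described as "a member of research staff skilled in using a handheld pressure algometer".
- 5RM: depends on effort and on how the test is run.
- Isometric mid-thigh pull (IMTP): read from force plates at 1000 Hz, but still depends on effort.

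PPT, 5RM and IMTP play no part in the rule that chooses the Phase Two pressure.

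**3. Illustration of how sensitive a trial of this size is**

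The bias itself cannot be estimated from the document. Suppose there is no true effect and open labels shift reported pain between arms by b standard deviations at every measurement. For the between-groups test of a repeated measures ANOVA:

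λ = f² × N × m / [1 + (m − 1)ρ], with 1 and N − 2 degrees of freedom.

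Inputs from the article: N = 24, m = 3 timepoints, two-sided alpha 0.05. Assumed: ρ = 0.5, which the article does not state.

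The formula first recovers the plan's own figure. With 0.64 entered as Cohen's f, λ = 0.4096 × 72 / 2 = 14.75 and power at N = 24 is 0.956, against a target of 0.95. The article labels 0.64 as d; that is a separate matter and does not affect this one.

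For a shift of b, f = b/2, so λ = (b²/4) × 72 / 2 = 9b².

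| Assumed b (SD) | λ | Chance of p < 0.05 |
|---|---|---|
| 0 | 0 | 5% |
| 0.1 | 0.09 | 6% |
| 0.2 | 0.36 | 9% |
| 0.3 | 0.81 | 14% |
| 0.5 | 2.25 | 30% |

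These values of b are assumptions. The table concerns the group effect averaged over timepoints; a shift that is constant over time would not appear in a group-by-time interaction.

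**The case against.** The best defence is that patients will feel the difference. The Abstract links 80% LOP with greater perceived discomfort, the study aims expect it to be less tolerable, and the selection rule treats low pressure as easier to tolerate. Each patient performs 7 sessions × 2 exercises × 4 sets = 56 sets under inflation, which is ample opportunity to form a view. This stands: a reader might infer that the pressure can simply be masked from patients, and the document does not support that. But a patient in a parallel-group trial has no second pressure to compare with, and feeling discomfort is different from being given a label and an expected direction.

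Three other strong readings also fail.

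- **That the PPT tester is a different person from whoever sets the cuff.** The article does not say who sets it. For anyone who both delivers treatment and collects outcomes, the statement that they are necessarily unblinded is correct. The article does not show that the two roles must be combined.
- **That masking assessors would protect the choice of Phase Two pressure.** It would not, because that choice rests on BPI and LEFS.
- **That participants are told their arm and the expected result.** The article says only that blinding is not feasible and that both pressures are described beforehand. The information sheet is not shown.

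The direction of bias is also uncertain: hoping for benefit from high pressure and disliking its discomfort could pull in opposite directions.

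**Conclusion.** The concern holds in limited form. The stated reason supports open allocation for participants in Phase Two and leaves it unsupported in Phase One, where set pressure is the only difference between arms. Withholding the label and the expected direction would reduce an avoidable source of expectation bias in the two self-reported outcomes that choose the Phase Two pressure, for all 28 planned Phase One patients. It would not remove the bias.

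The size is unknown. The illustration shows only that, if a shift of 0.2 to 0.5 SD arose with no true effect, the chance of a significant between-group result would rise from 5% to about 9% to 30%, given ρ = 0.5. The conclusion itself does not depend on those figures. It rests on the identical arm content, the self-reported outcomes and the selection rule, all of which are in the article. This is a worthwhile, inexpensive improvement, and does not show that the Phase One comparison is invalid.

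**What to change.** - Limit the statement that participants cannot be blinded to Phase Two.
- In Phase One, tell participants that they will receive one of two pressures, without disclosing the arm or the direction expected, and keep the set pressure out of their view.
- At the end of the intervention (day 5), ask participants to guess their arm, and report the guesses by arm. Read them descriptively, since a guess also reflects how much the patient felt they improved.
- List incomplete masking among the limitations.
- Where existing staffing allows, have PPT, 5RM and IMTP taken by a research team member who is not told the pressure. State that this protects secondary outcomes only.

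The cost is wording in the protocol and information sheet, placement of the device display, and one question on day 5. Sample size and treatment do not change. The assessor step depends on rostering, for which the article gives no staffing figures; PPT before, immediately after and 60 minutes after sessions makes it the hardest part. Masking remains imperfect, and the device operator stays unmasked.
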